## Abstract

**Background: **Rio de Janeiro and Niterói are neighbouring cities in southeastern Brazil which experience large dengue epidemics every 2 to 5 years, with >100,000 cases notified in epidemic years. Costs of vector control and direct and indirect costs due to the
*Aedes*-borne diseases dengue, chikungunya and Zika were estimated to total $650 million USD in 2016, but traditional vector control strategies have not been effective in preventing mosquito-borne disease outbreaks. The
*Wolbachia* method is a novel and self-sustaining approach for the biological control of
*Aedes*-borne diseases, in which the transmission potential of
*Aedes aegypti* mosquitoes is reduced by stably transfecting them with the
*Wolbachia* bacterium (
*w*Mel strain). This paper describes a study protocol for evaluating the effect of large-scale non-randomised releases of
*Wolbachia­*-infected mosquitoes on the incidence of dengue, Zika and chikungunya in the two cities of Niterói and Rio de Janeiro. This follows a lead-in period since 2014 involving intensive community engagement, regulatory and public approval, entomological surveys, and small-scale pilot releases.

**Method:** The
*Wolbachia* releases during 2017-2019 covered a combined area of 170 km
^2^ with a resident population of 1.2 million, across Niterói and Rio de Janeiro. Untreated areas with comparable historical dengue profiles and demographic characteristics have been identified
*a priori* as comparative control areas in each city. The proposed pragmatic epidemiological approach combines a controlled interrupted time series analysis of routinely notified suspected and laboratory-confirmed dengue and chikungunya cases, together with monitoring of
*Aedes*-borne disease activity utilising outbreak signals routinely used in public health disease surveillance.

**Discussion:** If the current project is successful, this model for control of mosquito-borne disease through
*Wolbachia* releases can be expanded nationally and regionally.

## Abbreviations

BG trap: BG-Sentinel trap; IBGE: Instituto Brasileiro de Geografia e Estatística (Brazilian Institute of Geography and Statistics); ITS: interrupted time series; MoH: Ministry of Health; PAHO: Pan American Health Organisation; PCR: polymerase chain reaction; qPCR: quantitative polymerase chain reaction; RCT: randomised controlled trial; SINAN: Sistema De Informação De Agravos De Notificação (Brazilian National Notifiable Diseases Information System); WHO: World Health Organisation

## Background

The global incidence of dengue has increased dramatically in recent decades. Although cases are underreported, it is estimated that 390 million dengue virus infections occur every year, and of these 96 million have clinical manifestations of dengue or severe dengue. Globally, 3.9 billion people in 128 countries are at risk of infection
^1^. The primary vector of dengue is the
*Aedes aegypti* mosquito, which is also capable of transmitting other arboviruses (i.e. mosquito-borne viruses) including chikungunya, Zika, yellow fever and Mayaro
^2^.

The first reported dengue outbreak in Brazil was in 1845, with subsequent outbreaks in 1880–1912 and 1916–1923
^2^. As a result of a coordinated effort from the Pan American Health Organization (PAHO) and the World Health Organization (WHO) to eradicate
*Ae. aegypti*, Brazil was considered free of the mosquito in 1955, but the vector was reintroduced into the country two decades later
^3^. In 1986, dengue virus serotype 1 (DENV1) was introduced to Rio de Janeiro and an estimated 1 million people were infected
^3,
4^. Since then, dengue has become a major public health problem. From 1986 to 1993, outbreaks occurred approximately every 2–5 years, and from 1993 dengue became endemic with seasonal peaks in cases during the rainy season (December to May), but with ongoing transmission throughout the year
^2,
3^. Between 2000 and 2007, more than 3 million dengue cases were reported (caused by DENV serotypes 1, 2 and 3) and in 2010, DENV4 re-emerged after 28 years of absence
^2^.

The recent introduction of Zika and chikungunya in dengue hyperendemic areas of Brazil has aggravated the situation. The overlapping clinical features, absence of serological assays for the Zika virus that can reliably distinguish between acute disease and past exposure, and the association of pregnancy-associated Zika virus infection with microcephaly and other neurologic complications represents a great challenge for public health that will require new strategies and innovations
^5,
6^.

Between 2016 and 2017, 762 deaths were attributed to severe dengue in Brazil
^7^. Additionally, in 2017, 127 deaths were confirmed to be caused by chikungunya. Yellow fever has spread from the North of Brazil to the Southeast over the last years, affecting humans and non-human primates. From July 2017 to April 2018, 1,266 cases of yellow fever including 415 deaths were confirmed in Brazil, with 223 cases and 73 deaths occurring in Rio de Janeiro State
^8^. No autochthonous cases were reported in Rio de Janeiro city or Niterói, although some residents from those cities acquired yellow fever while traveling to other places in Brazil. A mass vaccination campaign against yellow fever began in 2016.

The costs of vector control, direct medical costs, and indirect costs related to dengue, Zika and chikungunya in Brazil were estimated to be 2.3 billion Brazilian reais ($650 million USD) in 2016
^9^. In the absence of an effective vaccine for these arboviruses, disease prevention depends on vector control. Vector control guidelines in Brazil
^10^ are focused on elimination or larvicide treatment of mosquito breeding sites and the control of adult mosquito populations with insecticides sprayed as ultra-low volume. The limited potential of these traditional vector control strategies to achieve large-scale and sustained reductions in dengue incidence is evidenced by the continuing public health burden of dengue throughout endemic areas where these measures are routinely employed, and the lack of robust efficacy data from well-designed trials to inform their optimal implementation
^11^.

The
*Wolbachia* method (
www.worldmosquito.org) is a novel, natural, and self-sustaining approach to reduce arboviral diseases transmitted by
*Ae. aegypti* mosquitoes. The symbiotic
*Wolbachia* bacterium is found naturally in over 60% of insect species, but not in
*Ae. aegypti*, and is passed from one generation to the next through the insect’s eggs. Stable transinfection of
*Wolbachia* into a local
*Ae. aegypti* colony in the laboratory produces a lineage of
*Wolbachia-*carrying mosquitoes which, upon release over several weeks, can achieve dissemination of
*Wolbachia* into the local
*Ae. aegypti* population through the processes of maternal inheritance and cytoplasmic incompatibility that give
*Wolbachia*-carrying mosquitoes a reproductive advantage. The DENV-transmitting potential of mosquitoes stably transfected with
*Wolbachia*
*pipientis* (
*w*Mel strain) is reduced by 66–75%
^12,
13^, a phenotype which has been shown to persist in field mosquito populations up to five years after the end of releases. Mathematical modelling of this reduced transmissibility predicts a substantial and sustained reduction in dengue incidence in human populations where
*Wolbachia* is established
^13^. Laboratory data indicate a similar reduction in the competence of
*Wolbachia-*carrying
*Ae. aegypti* for transmitting other viruses including Zika, chikungunya, yellow fever and Mayaro
^14–
17^.

With releases now conducted in eight countries over the past eight years, the World Mosquito Program has demonstrated that
*Wolbachia* can be successfully established and maintained in both small-scale and large-scale urban settings in multiple ecological environments
^18–
22^.

A core objective of these releases has been to ensure strong community acceptance and government support for the approach, achieved through embedding community and stakeholder engagement within the project activities in each site. Observational evidence of the impact of
*Wolbachia* releases on arboviral disease in pilot sites has been encouraging, with no evidence of local dengue transmission where
*Wolbachia* has established at high levels. Following city-wide deployment in Townsville, Australia, there has been no confirmed local dengue transmission in
*Wolbachia*-treated areas for four seasons since completion of releases, despite local transmission every year for the prior 13 years and ongoing importation of DENV infection in travelers
^21^. A cluster randomized controlled trial (RCT) to generate a robust and quantitative estimate of the impact of
*Wolbachia* on dengue incidence commenced in Yogyakarta, Indonesia in 2017, with reporting of results expected in 2021
^23^.

In Brazil, planned scale up of
*Wolbachia* deployments from demonstration projects in Rio de Janeiro and Niterói to large-scale releases was accelerated by the declaration of Zika as a public health emergency by the WHO in early 2016, and the recommendation by WHO’s Vector Control Advisory Group in March 2016 that the
*Wolbachia* method be evaluated in rigorously monitored pilot deployments under operational conditions, to build evidence of epidemiological effectiveness against
*Aedes*-borne viruses
^24^. Given the imperative from stakeholders and funders to scale up deployment within a relative short time frame, and to retain sufficient flexibility to optimize methods for large-scale deployment in the varied micro-environments within Niterói and Rio de Janeiro, an RCT or other carefully controlled deployment was not considered feasible. Instead releases under operational conditions, and with pragmatic evaluation of disease impact using data routinely collected for public health purposes, was favoured. The primary reason that randomised deployment of the
*Wolbachia* intervention was not undertaken (either by random allocation of treated and untreated areas, or by randomising the sequence of staged deployments) was the intensive community engagement effort required in release areas in advance of deployments, as well as the gains in logistical efficiency and entomological outcomes from staging deployments across large contiguous areas. The potential benefits of randomised allocation of deployments in reducing bias from known and unmeasured confounders would require the intervention (and control) areas to be divided into a large number of units for randomisation. This fragmentation of the deployment areas would have made the community engagement activities and deployment logistics infeasible. Having small, fragmented release areas interspersed with untreated areas would also have greatly increased the potential for contamination between treatment arms from both mosquito movement and human movement, thereby diluting the observable intervention effect.

Here we describe a protocol for evaluating the effect of large-scale non-randomized
*Wolbachia* releases on the incidence of dengue, chikungunya and Zika in the cities of Niterói and Rio de Janeiro. The proposed strategy employs a controlled interrupted time series analysis of routinely notified suspected and laboratory-confirmed cases of dengue, chikungunya and Zika, together with monitoring of disease activity with outbreak signals routinely used in public health disease surveillance. This methodology allows measurement of the impact of the intervention at the population level over time, accounting for the seasonal trends and inter-annual fluctuations often observed in dengue and other mosquito-borne disease incidence.

## Methods

### Study design

The aim of this epidemiological study is to test the hypothesis that the establishment of
*Wolbachia* in local
*Ae. aegypti* populations in Rio de Janeiro and Niterói leads to a reduction in the burden of
*Aedes*-borne disease.

The impact of
*Wolbachia* deployment on disease incidence will be evaluated using routine notifiable disease surveillance data to describe associations between temporal and spatial trends in dengue, chikungunya and Zika and the deployment of
*Wolbachia* across Niterói and Rio de Janeiro, with two objectives:

1. Estimate the reduction in dengue, chikungunya and Zika in the aggregate treated areas of Niterói and Rio de Janeiro compared to an untreated control area, and in each treated zone compared to the untreated control area, each year for five years after
*Wolbachia* establishment.2. Quantify the occurrence of dengue outbreak signals in
*Wolbachia* treated areas compared to untreated areas in Niterói and Rio de Janeiro, for five years after
*Wolbachia* establishment, using outbreak indicators employed routinely for public health monitoring of dengue activity: i) control diagrams comparing the weekly dengue incidence (five-week moving average) against the five-year historical average in that same area; and ii) outbreak incidence threshold of 300/100,000 population in any month.

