### Wolbachia release and monitoring

Staged
*w*Mel
*Wolbachia*-mosquito deployments will be implemented in Niterói and Rio de Janeiro, in order to achieve
*Wolbachia* establishment across the two cities. Pilot releases commenced in late 2015, and city-wide deployments are ongoing through to the end of 2019.
*Wolbachia*-containing adult mosquitoes will be released at one location per 50 x 50 meter grid square for a minimum of 16 consecutive weeks in each release zone. In areas where
*Wolbachia* frequency remains low after 16 weeks of releases, or where particularly high wild type
*Ae. aegypti* populations are observed,
*Wolbachia*-containing mosquito eggs will also be released to complement adult releases with the aim of accelerating
*Wolbachia* establishment. Monitoring of
*Wolbachia* frequency will be done using BG-Sentinel mosquito traps (BioGents, Germany), distributed throughout the release area at a density of 16 traps per km
^2^. Traps will be serviced weekly and all collected mosquitoes identified morphologically by microscopy. From eight weeks after the start of releases, a maximum of 10
*Ae. aegypti* (male and female) per trap will be tested individually for
*Wolbachia* using quantitative polymerase chain reaction (qPCR).
*Wolbachia* screening will be performed biweekly during releases and until establishment, then every 1–3 months thereafter. All surplus
*Ae. aegypti* will be biobanked. Mosquito collection and screening results will be stored in a custom designed web-based data repository. The
*Wolbachia* prevalence in screened
*Ae. aegypti* will be reported aggregated to each release zone, calculated as the total number of
*Ae. aegypti* mosquitoes that tested positive for
*Wolbachia* aggregated across all BG traps in the zone, divided by the total number of
*Ae. aegypti* that were screened in that zone.

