Chikungunya diagnoses can be confirmed either through PCR or serology, as it does not cross-react with Zika or dengue. The proportion of notified cases with supportive laboratory findings is higher than for dengue: 31.9% and 18.2% in Rio and Niterói, respectively, in 2016.

Anonymized disaggregate (line-listed) data on notified suspected and laboratory-confirmed dengue, chikungunya and Zika cases will be extracted from the SINAN system for the historical pre-intervention period (2000–2016 for dengue, and 2015–2016 for chikungunya and Zika) and the prospective post-intervention period (2017–2023). The dataset will include age, sex, neighbourhood of primary residence, date of illness onset, date of notification, reporting health clinic, disease severity, hospitalisation, death, and where available, geocoordinates of primary residence, type of diagnostic test performed, diagnostic test result, and final diagnostic classification. Population data from the Brazilian census (IBGE) and population by neighbourhood of residence obtained from the cities of Rio and Niterói will be used to estimate the population in each release zone. The incidence rate (number of new dengue, Zika or chikungunya cases divided by the population at risk) will be expressed per 100,000 inhabitants.

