*Wolbachia* prevalence in the local mosquito population. The outcome distribution is assumed to be negative binomial to allow for overdispersion. Robust standard errors will be used to account for autocorrelation and heteroskedasticity. If an excess of zero counts is apparent, the proposed negative binomial model will be nested within a zero-inflated negative binomial model of the same structure. A likelihood ratio test can be performed to test model fit.

Separate analyses will be performed for each release zone compared with its pre-defined control area, and for the aggregate release areas in each city compared with the control area for each city. The availability of comparative control areas – well-matched to the release area in demographic characteristics and historical arboviral disease incidence (
Figure 2 and
Figure 3) – permits a robust, controlled analysis in which the confounding effects of seasonality and inter-annual variability can be adjusted for. The intervention effect will be estimated after 12 months of post-release observations have accumulated, and each 12 months thereafter for five years using cumulative post-release observations, for each release zone individually and in aggregate for each city.

Power was estimated for the ITS analysis using 1000 simulated datasets drawn from a negative binomial distribution fitted to a ten-year time series (2007–2016) prior to
*Wolbachia* deployment, of monthly dengue case notifications from release and control zones in Niterói and Rio de Janeiro. The simulated time series of dengue case numbers in the control zones as well as the pre-
*Wolbachia* release dengue case numbers in the treated zones were drawn directly from this model-generated distribution. Post-

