### Current study status

This study is ongoing.
*Wolbachia* releases are expected to be completed by the end of 2019, and the collation and analysis of disease surveillance data will continue until 2023.

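### Annual estimates are promised for five years in every release zone, but a zone finishing at end-2019 has at most four years of data before the 2023 cut-off

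*Protocol article*

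**What the plan says.** All the relevant statements are in the Methods of the protocol article.

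- **Horizon, Study design, objective 1:** estimates for the aggregate treated areas and "in each treated zone compared to the untreated control area, each year for five years after" Wolbachia establishment.
- **Horizon, Controlled interrupted time series analysis:** "The intervention effect will be estimated after 12 months of post-release observations have accumulated", and then "each 12 months thereafter for five years using cumulative post-release observations, for each release zone individually and in aggregate for each city".
- **End of releases, Wolbachia release and monitoring:** "city-wide deployments are ongoing through to the end of 2019". Adult mosquitoes are released "for a minimum of 16 consecutive weeks in each release zone".
- **End of releases and of data, Current study status:** "releases are expected to be completed by the end of 2019, and the collation and analysis of disease surveillance data will continue until 2023".
- **Extraction window, Epidemiological data sources:** "the prospective post-intervention period (2017–2023").

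Neither statement of the horizon is qualified by availability of data or by the zone's completion date. Objective 2 uses the same five years but speaks of treated areas without naming each zone, so the point rests on objective 1 and the time series section.

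**The concern.** The horizon and the calendar are both fixed in the text, and for late-finishing zones they do not fit together. This is a conflict between stated figures, not detail left to a fuller document.

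Two things are at stake. First, the fifth annual estimate cannot be produced for such zones. The Discussion says that epidemics come every 2 to 5 years, so a lost year may decide whether a zone's follow-up includes an epidemic season. Second, the protocol does not say when the post-period begins for a city aggregate made of zones treated at different times. Later-year aggregate estimates could then carry very unequal follow-up from zones that differ a good deal: Table 1 gives densities from 1,357 to 14,197 per km² across the Niterói zones and from 4,496 to 18,394 across the Rio de Janeiro zones. A reader would see only one city-level label.

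**Working it through.** **Inputs.** Promised horizon: 5 years (Study design; time series section), read as looks at 12, 24, 36, 48 and 60 months. End of releases: end of 2019. End of data: 2023, with no day given. Minimum release: 16 weeks. Zone populations: Table 1.

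**Step 1. Follow-up for a zone finishing at end-2019.** Follow-up = end of data − start of clock.

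| Start of clock | Data to 1 Jan 2023 | Data to 30 Jun 2023 | Data to 31 Dec 2023 |
|---|---|---|---|
| Start of a final 16-week release (about 10 Sep 2019) | 3.3 | 3.8 | 4.3 |
| End of releases, 31 Dec 2019 | 3.0 | 3.5 | 4.0 |
| Establishment 6 months later (assumed) | 2.5 | 3.0 | 3.5 |
| Establishment 12 months later (assumed) | 2.0 | 2.5 | 3.0 |

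The stated 5 years is not reproduced in any cell. The documents give no lag to establishment, so the last two rows are illustrations. Establishment during releases is also possible. For a release of minimum length, the first row bounds that case at 4.3 years, which is still four complete annual looks.

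**Step 2. Which zones can reach five years.** 31 Dec 2023 − 5 years = end of 2018. Zones completed or established by then can reach five years if the data run to the end of 2023. A first zone finishing on 23 April 2017 (assumed: 16 weeks from 1 January 2017) would have 6.7 years.

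**Step 3. When data would have to end.** End-2019 + 5 years = end of 2024. With the assumed lag of 6 to 12 months, mid-2025 to end-2025.

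**Step 4. City aggregate.** The control area's post-period starts with that of its comparative release zone; no start is given for the aggregate.

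- If the clock starts when the whole city is complete at end-2019, the limit is that of Step 1: 4.0 years.
- If it starts with the first zone, five years may be reached, with unequal contributions. With the assumed April 2017 completion, the five-year mark falls in April 2022. A zone finishing at end-2019 then contributes about 2.3 years (end-2019 to late April 2022) against 5.0 for the first zone.

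**Step 5. Share of treated residents affected.** Completion dates by zone are not given. Assume that zones finish in numeric order, and vary how many finish after end-2018.

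| City | Last zone only | Last two zones |
|---|---|---|
| Rio de Janeiro | 220,739 / 886,551 = 25% | (408,036 + 220,739) / 886,551 = 628,775 / 886,551 = 71% |
| Niterói | 101,784 / 373,117 = 27% | (178,891 + 101,784) / 373,117 = 280,675 / 373,117 = 75% |

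**The case against.** The best defence is that little of importance turns on the fifth year. The power simulations cover one to three years after the intervention and claim 80% power at two years (for a 60% reduction) and at three years (for 50%). The Dissemination section plans the report two years after releases end, about end-2021. Both fit inside the window. The end of releases is only an expected date, and early zones can reach five years. All of this stands and limits the severity, but it does not remove the conflict, because five years is promised for each zone.

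A reader might also infer more than the documents support.

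- **That the city aggregates certainly stop at four years.** No section sets the start of the aggregate clock, and the data section calls 2017 to 2023 as a whole the post-intervention period. Both cities also share one stated end date, so one of them may finish earlier. The four-year limit on the aggregate is conditional.
- **That fourth- and fifth-year city estimates would rest on early zones alone.** The estimates use cumulative observations, so late zones still contribute, with fewer months. A zone finishing at end-2019 with no lag reaches year four if the data run through December 2023.
- **That about three quarters of treated residents are affected.** That needs numeric order and also the last two zones both finishing after end-2018. The documents state neither.

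**Conclusion.** The point holds for late-finishing zones. On the protocol's own dates, a zone whose releases end at end-2019 falls at least one year short of the promised five: at most 4.0 years after releases, and less if establishment comes later or the data stop before December 2023. The fifth annual estimate is the certain loss. The fourth is lost only with an establishment lag or an earlier cut-off in 2023.

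For the aggregates, the defect is an undefined start. A start at completion of the whole city brings the same four-year limit, while an earlier start brings unequal zone contributions. The share of residents affected is unknown, with 25% to 71% in Rio de Janeiro and 27% to 75% in Niterói as illustrations under numeric order.

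Severity is moderate. It would be wrong to conclude that the primary endpoint, the model, the power statement or the planned two-year report is undermined; none of them depends on the fifth year.

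**What to change.** Reconcile the Study design and time series sections with the data-source and status sections in one of two ways.

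1. **Extend the data.** Continue the extraction from the national surveillance system to five years after establishment in the last zone: at least end-2024 if releases end at end-2019, and later by any lag to establishment. This costs one or two further routine extracts and no field work.
2. **Restate the horizon.** Promise up to four years for zones finishing in 2019, and five only where completion or establishment is by end-2018. This costs a change of wording and a shorter stated horizon for late zones.

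In either case, state when the post-period starts for each city aggregate, and report the zones and the population contributing to each year's estimate. Both need only completion or establishment dates by zone, which the release monitoring should supply.

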### Dengue outbreak signals

As a complementary approach for evaluating the public health impact of large-scale
*Wolbachia* releases, we will also use the following dengue outbreak alert tools routinely used in public health practice. We hypothesise that these dengue outbreak signals will not be triggered in areas where
*Wolbachia* has been established.

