**1. Control diagram (endemic channel)**

The definition of a dengue outbreak or epidemic has changed over time in Brazil. In Rio de Janeiro and Niterói, a control diagram is currently used to monitor dengue incidence. Briefly, the control diagram is constructed from a five-week centered moving average of weekly notified dengue incidence for the past five years excluding epidemic years. An early signal of a dengue outbreak/epidemic is triggered when the weekly incidence of dengue crosses the upper limit of the control diagram
^26^, with the upper limit defined as [mean+(standard deviation*1.96)]. Incidence that remains above the upper limit of the control diagram for two or more consecutive weeks constitutes a dengue outbreak. For the purpose of monitoring the impact of
*Wolbachia* releases on dengue, we will construct annual control diagrams with weekly dengue incidence, by city and for each release and non-release zone, to monitor the occurrence of dengue outbreaks. The number of dengue outbreak signals triggered per year will be reported.

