**2. Classical incidence threshold**

Another outbreak definition that has been used by the Ministry of Health (MoH) in previous years
^20,
22,
23^ is a dengue incidence threshold of ≥300 cases/100,000 population in a given month. Although not included in current MoH guidelines, this provides an alternative endpoint for evaluating dengue activity at a population level in the post-intervention period, compared with pre-intervention, and we will report the number of months in a given year where dengue incidence crosses this threshold.

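### Both objectives are timed from Wolbachia establishment, and the outbreak-signal hypothesis is limited to it, although it is a result of the releases; the methods count by release zone and post-release period instead

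*Protocol article*

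**What the plan says.** All references are to the protocol article.

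- **Study design, objective 2.** Signals are compared between "treated areas compared to untreated areas in Niterói and Rio de Janeiro, for five years after"; the event that starts the five years is Wolbachia establishment. The areas are defined by treatment and the clock by establishment. Objective 1 in the same section has the same five-year establishment clock.
- **Dengue outbreak signals.** The hypothesis is conditional: "We hypothesise that these dengue outbreak signals will not be triggered in areas where" Wolbachia has become established.
- **Control diagram (endemic channel).** "we will construct annual control diagrams with weekly dengue incidence, by city and for each release and non-release zone". Establishment is not a condition.
- **Classical incidence threshold.** The threshold is meant for "evaluating dengue activity at a population level in the post-intervention period, compared with pre-intervention". Again establishment is not a condition.
- **Controlled interrupted time series analysis.** "The intervention effect will be estimated after 12 months of post-release observations have accumulated", and yearly after that. The control area's post-intervention period starts with that of its release zone. This alignment is stated for the ITS only.
- **Wolbachia release and monitoring.** Egg releases are added where frequency is still low after 16 weeks, "or where particularly high wild type" Ae. aegypti populations are seen. Prevalence is reported for each release zone.

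**The concern.** Establishment is an outcome of the intervention, observed while disease data accrue, and only release areas can reach it. Starting the treated clock there, or testing the hypothesis only there, selects treated time on a post-deployment result. The control side has no matching selection.

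The article foresees uneven uptake, since it plans supplementary releases for areas with low frequency or many wild-type mosquitoes. The Discussion goes on to envisage expanding the model to the rest of the country and the Americas. That decision concerns a programme of releases, including places where uptake is slow or poor. A count of signals conditional on establishment answers a narrower question.

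**Working it through.** The plan gives no sample size or power figure for the outbreak signals. Its 80% power statement belongs to the ITS, so there is no figure to reproduce.

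**1. The start of treated time in each place**

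| Section | Areas | Start or condition |
|---|---|---|
| Study design, objectives 1 and 2 | treated areas (objective 1 also by zone) | establishment |
| Dengue outbreak signals, hypothesis | established areas | establishment reached |
| Control diagram | every release and non-release zone | annual, no condition |
| Incidence threshold | population level | post-intervention |
| ITS | every zone, and city aggregate | post-release |

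The first two rows do not agree with the last three. Under the first two rows taken literally:

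- a zone that never establishes has no start date, so it has no objective 2 window;
- a slow zone enters late, and its earlier post-release signals are not counted. Releases run to the end of 2019 and data to 2023, about four years, so late entry is not made up at the end;
- an outbreak in a zone that has not established cannot contradict the hypothesis.

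**2. How much one zone can weigh (Table 1)**

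- Niterói: 23,747 + 68,695 + 178,891 + 101,784 = 373,117, the stated total. Zone 3: 178,891 / 373,117 = 47.9%.
- Rio de Janeiro: 107,130 + 150,646 + 408,036 + 220,739 = 886,551, the stated total. Zone 3.1: 408,036 / 886,551 = 46.0%.
- The smallest shares are 6.4% (Niterói Zone 1) and 12.1% (Rio Zone 1).

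**3. Illustration if Wolbachia works where established**

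Assumptions: the signal ratio against control is RR in established zones and 1 in the others; k of 4 equally weighted zones fail. RR = 0.5 is one of the incidence effects in the article's power simulation, borrowed here as a signal ratio.

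Ratio over all release zones = (k + (4 − k) × RR) / 4. The established-only ratio is RR.

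- k = 1: (1 + 3 × 0.5) / 4 = 0.625, against 0.50.
- k = 2: (2 + 2 × 0.5) / 4 = 0.75, against 0.50.

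Weighted by population with one zone failing, ratio = share + (1 − share) × 0.5:

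- Niterói: from 0.064 + 0.936 × 0.5 = 0.53 (Zone 1) to 0.479 + 0.521 × 0.5 = 0.74 (Zone 3).
- Rio: from 0.121 + 0.879 × 0.5 = 0.56 (Zone 1) to 0.460 + 0.540 × 0.5 = 0.73 (Zone 3.1).

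**4. Illustration if there is no effect**

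Assumptions: failing zones have h times the baseline signal risk of the other zones, and control equals the average of all release zones. Established-only ratio = 4 / (k × h + 4 − k). With k = 1:

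- h = 0.5: 4 / 3.5 = 1.14
- h = 1: 4 / 4 = 1.00
- h = 2: 4 / 5 = 0.80
- h = 3: 4 / 6 = 0.67

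The documents do not give h. The direction is therefore open when there is no effect.

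**The case against.** The strongest reply is that nothing in the article removes a zone. Objective 2 speaks of treated areas, and Table 1 lists all eight release zones as the treated side. Control diagrams are planned for each of them, and threshold months are tied to the post-intervention period. Objective 1 carries the same establishment wording, yet its method is timed from release, which suggests loose drafting more than a deliberate filter. The hypothesis can be read as a biological prediction, not a counting rule. The extra egg releases aim to bring difficult areas to establishment and do not forecast failure. Outbreak signals are a complementary approach. The primary endpoint is analysed by ITS for every zone and city, with an added analysis by measured Wolbachia frequency. A numerical definition of establishment may properly sit in the full protocol.

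Most of this stands. A reader might infer that zones which fail or are slow will leave the treated arm, and that the comparison therefore favours the intervention. The documents do not support that: exclusion is not stated, slow zones enter late and do not leave, and lost lead-in time need not bias a comparison whose control weeks are aligned. Nor do the two objectives differ in their stated clock. The missing cut-off is no part of this point.

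The control-diagram section does not settle the matter, however. It says which zones are charted, but not when treated time begins or which signals test the hypothesis. Alignment of the control weeks is stated for the ITS only.

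**Conclusion.** The point holds as an inconsistency with a possible consequence. The objectives and the hypothesis depend on a post-deployment result, while the methods count by release zone and by post-release or post-intervention period. This leaves room to omit treated zones or time from objective 2 without departing from its wording.

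If Wolbachia protects where established, the omitted zones and time are the less protected ones, and signals under a release programme would probably be understated. With RR 0.5 and one of four equally weighted zones failing, the ratio reads 0.50 where all release zones give 0.625. With no effect, the direction is unknown: 0.67 to 1.14 for h from 3 to 0.5. All these ratios rest on the assumed k, h and RR; only the population shares come from the plan. The primary ITS analysis, which uses post-release observations, is not undermined. The change is worth making because it is cheap and removes selection on a post-release result.

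**What to change.** - **Main comparison for objective 2.** Count signals in all pre-defined release zones, whatever Wolbachia frequency they reach. Start from a fixed release-based date that matches the ITS post-intervention period, and count the control area over the same calendar weeks.
- **Secondary comparison.** Report the established-only result, with each zone's Wolbachia frequency beside its signal count.
- **Wording.** In Study design, give both objectives the release-based start. In Dengue outbreak signals, state the main hypothesis for all release zones and keep the prediction for established areas as secondary.

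The zone-level diagrams and the prevalence data are already planned, so the cost is rewording and one additional tabulation. The downside is that the main result may look less favourable than one restricted to established areas.
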